### Safety Variables

The safety evaluation variables in this study will include the frequency of adverse events, vital signs, and suicide risk assessment. All adverse events that occur during the clinical trial will be assessed for their severity and the causal relationship with the intervention, and their frequency will be used as an evaluation variable. If clinically significant adverse events are observed, changes in vital signs will be assessed compared to preintervention values. The C-SSRS will be used to evaluate the risk of suicide in participants, and a score of 4 or higher will be considered indicative of a suicide risk.

### Exploratory Variables

The exploratory variables in this study will include the Emotional Reactivity Test, Empathy Quotient (EQ), Perceived Stress Scale (PSS), and Heart Rate Variability (HRV). The Emotional Reactivity Test, EQ, and PSS will be assessed at baseline and at week 8, while HRV will be assessed at baseline, week 4, and week 8.

The Emotional Reactivity Test is a behavioral assessment that measures an individual’s responses to both positive and negative emotional stimuli. This test is designed to assess the phenomenon of emotional contagion by observing changes in facial expressions in response to emotional stimuli. It is based on experimental models from past research on emotion processing [30,31]. Participants are shown video clips that comprise 4 emotional contexts (joy, sadness, fear, anxiety, and neutral) and their facial expressions are recorded while they watch the emotional stimulus clips. Following the recording phase, participants will report the degree of their emotional state in response to the emotional stimuli on a scale of 0-9 using E-Prime software (Psychology Software Tools). Facial expressions will be analyzed using iMotion software (iMotions A/S).

The electrocardiography signal will be recorded using electrodes placed on the participant’s chest. Heart rate and R-R intervals will be extracted from the electrocardiography data using an in-house script developed in MATLAB (2016b, The MathWorks, Inc). The time-domain HRV metrics will include the mean R-R interval, the SD of R-R interval, and the root-mean-square of successive differences. The frequency-domain HRV metrics that will be calculated include the low-frequency power (0.04-0.15 Hz), high-frequency power (0.15-0.4 Hz), and the normalized low- and high-frequency power following standard recommendations [32].

### Sample Size

Considering the absence of prior clinical trials proving the therapeutic effect of electroacupuncture in anxiety disorders compared to a control group, this study references preliminary research recommending a minimum of 15 participants per group to ensure feasibility and facilitate exploratory analyses [33]. Therefore, to accommodate potential variances and ensure statistical robustness, we plan to enroll 15 participants per group, for a total of 45 participants. However, to enhance statistical rigor and account for potential attrition, the final sample size was adjusted to 20 participants per group, yielding a total of 60 participants.

### Randomization and Allocation

In this study, participants will be randomly assigned to one of the 3 groups: the EA-VNS group, the EA-MNS group, or the usual care group. Stratified block randomization will be used, using SAS software (version 9.4 or higher, SAS Institute), to ensure an unbiased and equal allocation (1:1:1 ratio) across the groups. The stratification criteria will include the specific type of anxiety disorder diagnosed in each participant, such as panic disorder, agoraphobia, generalized anxiety disorder, social anxiety disorder, and other specified anxiety disorders. This method ensures proportional representation of each anxiety disorder subtype within each study arm, thereby controlling for variability in treatment response based on the type of anxiety disorder. The randomization list in this study will be held by an independent statistician and will not be disclosed to ensure confidentiality. The randomized codes will be placed in opaque, sealed envelopes and stored in a locked cabinet. Randomization envelopes will be opened in the order of participant enrollment to assign each group. The opened envelopes will be stored separately, and the date, time of opening, and the opener’s signature will be recorded on the envelopes.

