### Study Populations

To ensure the safety of participants and the integrity of study outcomes, specific inclusion and exclusion criteria were applied. These criteria were designed to select individuals with appropriate clinical characteristics for the study intervention while minimizing potential risks and confounding variables. Eligible participants were required to meet all inclusion criteria and none of the exclusion criteria listed in Textbox 1.

Inclusion and exclusion criteria.Inclusion criteria:(1) Aged 19-70 years, as individuals aged 19 years and older are legally permitted to provide autonomous consent to participate in clinical research in Korea.(2) Diagnosed with an anxiety disorder including social anxiety disorder, panic disorder, agoraphobia, generalized anxiety disorder, other specified anxiety disorders, and unspecified anxiety disorder as assessed through the Structured Clinical Interview for *DSM-5* (*Diagnostic and Statistical Manual of Mental Disorders* [Fifth Edition]; SCID-5).(3) Voluntarily decided to participate in this study and signed the written consent form.(4) Able to complete electroacupuncture-neural stimulation treatments over 8 weeks.Exclusion criteria:(1) At high risk of suicide as assessed by the Columbia-Suicide Severity Rating Scale with a score of 4 or more.(2) With a history of schizophrenia or bipolar disorder.(3) Diagnosed with separation anxiety disorder, selective mutism, substance-induced anxiety disorder, anxiety disorder due to medication, or anxiety disorder due to other medical conditions.(4) Received acupuncture treatment within the last 4 weeks.(5) With a history of alcohol or other substance use disorders within the last 8 weeks.(6) With a history of cerebrovascular disease, brain tumor, or traumatic brain injury.(7) With a history of neurological or systemic disease that may affect the central nervous system.(8) In medical conditions requiring inpatient treatment.(9) Usage of a pacemaker.(10) With contraindications to acupuncture treatment (eg, acupuncture-associated vasovagal response or tissue damage due to acupuncture).(11) Taken medication or participated in another clinical trial within the last month.(12) Pregnant or lactating women, or those not using medically acceptable methods of contraception during the study period.(13) Deemed inappropriate for enrollment due to other reasons as determined by the investigators.

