### Statistical Methods: Definition of the Analysis Set

The analysis sets for evaluating data obtained in this clinical trial are defined as follows: the Full Analysis Set is in accordance with to the intent-to-treat principle, encompassing all participants who met the inclusion and exclusion criteria, were randomly assigned, and for whom baseline measurements and at least 1 postbaseline primary outcome was obtained. The Per Protocol Set (PPS) includes participants from the FAS who have adhered to at least 75% of the total intervention and do not meet any discontinuation or dropout criteria. The Safety Analysis Set (SAS) comprises all participants who have undergone at least one safety assessment following random assignment.

All data, including efficacy outcomes, will be analyzed using the FAS, with the PPS serving as a secondary analysis group for additional analyses. Safety variables will be analyzed using SAS. Continuous data will be presented as means and confidence intervals, while categorical data will be presented as frequencies and percentages (%). If necessary, initial characteristics of participants measured at screening or baseline may be categorized for subgroup analysis.

Unless specifically stated otherwise, all statistical analyses in this study's results will be conducted as 2-sided tests, with a significance level set at 5%. However, for the analysis of the primary outcome, the significance level will be set at 2.5%. Statistical analyses will be performed using SAS software (version 9.4 or higher, SAS Institute).

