### Statistical Methods for Analyzing Efficacy Outcomes

#### Primary Outcomes

The primary outcome analysis will use a mixed-effect model repeated measure (MMRM) approach, including each treatment group and visit time point as fixed factors, with participants as random factors, and accounting for interactions between groups and visit time points. Variables that show statistically significant differences in demographic or sociological characteristics, or other factors potentially influencing anxiety disorders, will be incorporated as fixed factors. Results will be presented with means, 97.5% CIs, and *P* values. In addition, if significant baseline differences exist between groups, an Analysis of Covariance (ANCOVA), adjusted for baseline values as a covariate, will be conducted.

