### Statistical Analysis of Demographic and Baseline Characteristics

In this study, descriptive statistics for demographic and pretreatment characteristics will be presented for each group. Continuous variables will be analyzed using either ANOVA or the Kruskal-Wallis test, depending on the data distribution. Categorical variables will be analyzed using the chi-square test or Fisher exact test; Fisher exact test will be applied when more than 25% of cells in a contingency table have an expected frequency of less than 5. If necessary, significant differences in baseline characteristics between groups will be adjusted for by incorporating these characteristics as covariates in the efficacy variable analysis.

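### Randomisation is stratified by anxiety-disorder type, but the primary model does not commit that factor as a term; if disorder type predicts HAM-A change, precision and power are lost

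*Protocol article*

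**What the plan says.** Randomization and Allocation describes stratified block randomisation, 1:1:1, and states that "The stratification criteria will include the specific type of anxiety disorder diagnosed in each participant". Five types are then listed after the words 'such as': panic disorder, agoraphobia, generalised anxiety disorder, social anxiety disorder and other specified anxiety disorders. The reason given is proportional representation of each subtype in each arm, "thereby controlling for variability in treatment response based on the type of anxiety disorder".

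The primary-outcome paragraph of the statistical methods describes the MMRM as "including each treatment group and visit time point as fixed factors, with participants as random factors", plus the group-by-visit interaction. On further terms it says: "Variables that show statistically significant differences in demographic or sociological characteristics, or other factors potentially influencing anxiety disorders, will be incorporated as fixed factors". The section on demographic and baseline characteristics adds that, if necessary, "significant differences in baseline characteristics between groups will be adjusted for by incorporating these characteristics as covariates".

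On the error rate, tests in general "will be conducted as 2-sided tests, with a significance level set at 5" per cent, but "for the analysis of the primary outcome, the significance level will be set at 2.5" per cent. There are two primary comparisons, each electroacupuncture arm against usual care, with 20 participants per arm.

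**The concern.** The design and the analysis treat disorder type differently. The design treats it as related to outcome and forces balance on it. The analysis neither names it nor gives a rule likely to bring it in. Forced balance removes the between-diagnosis component from the true sampling error of the arm difference. A model without the factor still counts that component as residual variance. The reported standard error then exceeds the true one, the confidence interval is too wide, and the test runs below its nominal level.

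The rule for adding covariates makes matters worse for this factor. A trigger based on baseline significance selects variables that happen to be imbalanced, and stratified blocks exist to prevent imbalance in diagnosis. In a trial with 20 per arm and a 2.5% threshold, little precision can be spared.

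**Working it through.** **The plan's own figure.** The article gives no power, effect size or SD, so there is no power calculation to reproduce. The sample-size arithmetic is consistent (3 × 15 = 45; 3 × 20 = 60), and 0.05 / 2 = 0.025 matches two primary comparisons.

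**Inputs from the article.** 20 per arm; 1:1:1 stratified blocks; five named disorder types; two-sided 2.5% per comparison.

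**Assumptions (not in the article).** R² is the share of the within-arm variance of week-8 HAM-A change explained by disorder type, taken from 0 to 0.30. The true effect is 0.8 or 1.0 SD. Blocks are of 3 or 6, and the strata are equal or skewed.

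**Baseline precision.** With SD = 1, the model without stratum reports SE = √(2/20) = 0.316. The two-sided 2.5% critical value is 2.241.
- Power at 0.8 SD: Φ(0.8/0.316 − 2.241) = 61%.
- Power at 1.0 SD: Φ(1.0/0.316 − 2.241) = 82%.
- Difference detectable with 80% power: (2.241 + 0.842) × 0.316 = 0.98 SD.

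**Effect of leaving the stratum out.** With balanced strata the true SE is about 0.316 × √(1 − R²), while the reported SE stays at 0.316. The actual type I error is then about 2 × [1 − Φ(2.241/√(1 − R²))].

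| R² | True SE | Reported/true | Type I error, formula | Type I error, simulated |
|---|---|---|---|---|
| 0 | 0.316 | 1.00 | 2.5% | 2.4% |
| 0.05 | 0.308 | 1.03 | 2.1% | 2.0% |
| 0.10 | 0.300 | 1.05 | 1.8% | 1.8% |
| 0.20 | 0.283 | 1.12 | 1.2% | 1.3% |
| 0.30 | 0.265 | 1.20 | 0.7% | 0.8% |

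The simulated column uses a linear model of week-8 change, 60 participants, five equal strata, blocks of 3, complete data and 6,000 trials per row. With the stratum in the model, type I error stayed at 2.2–2.6%.

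**Power without → with the stratum (simulated, equal strata).**

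| R² | Effect 0.8 SD | Effect 1.0 SD | Loss, points |
|---|---|---|---|
| 0 | 59.8% → 59.4% | 80.2% → 80.2% | about 0 |
| 0.05 | 59.9% → 62.1% | 79.6% → 81.0% | 1–2 |
| 0.10 | 59% → 64% | 81.0% → 83.9% | 3–5 |
| 0.20 | 59% → 69% | 83.1% → 89.4% | 6–10 |
| 0.30 | 60% → 76% | 82.9% → 92.4% | 10–16 |

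These runs used 4,000 to 5,000 trials each, so differences of about 1 point are within simulation error. Blocks of 6 (equal strata) and a skewed mix (blocks of 3) gave similar results.

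**Would the baseline-significance rule select diagnosis?** A chi-square test of diagnosis by arm at 5% was applied to 60 participants in five strata with blocks of 3. It selected diagnosis in 0 of 40,000 trials with equal strata and in 0 of 40,000 with a skewed mix (6/5/25/16/8).

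**Where the factor must enter.** HAM-A is measured at baseline, week 4 and week 8. Suppose baseline is one of the repeated visits and stratum s shifts the level by a constant δₛ. In the week-8 minus baseline difference, δₛ − δₛ = 0. A constant shift therefore does no harm to the change contrast, and a stratum main effect does nothing for it with complete data. Only a stratum effect on change matters, and in that model it needs a stratum-by-visit term. If the response is change from baseline, the figures above apply directly.

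**Cost when diagnosis is not prognostic.** In a less favourable layout (strata 26/16/10/5/3, 51 analysed, 0.8 SD, R² = 0), power went from 50.3% to 48.8% when the stratum was added, a loss of 1.5 points. At R² = 0.10 the same layout gained, from 50.6% to 53.9%.

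**The case against.** The strongest reply is that the stratum is not excluded. The covariate sentence also mentions other factors that may influence anxiety disorders, and disorder type is an obvious candidate. On one reading that phrase is a separate route needing no significance test. On the other it is governed by the words about significant differences, which the baseline-characteristics section supports. The text does not settle which is meant. A reader might infer that the plan drops the stratum outright; the documents do not support that. What stands is that no sentence commits it, and that under the looser reading its inclusion is an open choice in the primary analysis.

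Second, the size depends on an R² that the documents do not give, and it may be nil. That stands, and it is why the range starts at 0.

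Third, if baseline is a repeated visit, stable differences between diagnoses cancel from the change contrast. That also stands, and it alters the fix.

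Fourth, the article condenses a fuller protocol, and a full covariate list may sit there or in the analysis plan. That is fair as far as missing detail goes. But the article does state the model terms and a selection rule, and that rule works against this particular factor.

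Finally, eligibility covers "other specified anxiety disorders, and unspecified anxiety disorder", whereas the named strata stop at other specified disorders. A reader might infer that unspecified cases have no stratum. The list follows 'such as', so it may be illustrative. How participants with two diagnoses are placed is operational detail that an article may leave out. Both points are minor.

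**Conclusion.** The point holds in a conditional form. The protocol stratifies on disorder type because it expects response to vary by type, yet the primary model does not commit that factor, and the stated trigger for adding covariates would almost never select it. If disorder type explains about 20% or more of the variance in HAM-A change, leaving it out costs about 6 to 16 points of power over the range examined. At 5 to 10% the cost is about 1 to 5 points, and at zero there is none.

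Three stronger inferences are not supported. The documents do not show that the standard errors will be too large, because that depends on an unstated R². Omission does not bias the estimate or inflate type I error; the error is conservative. And no stated power figure is wrong, because none is stated.

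The figures assume complete data, change as the response and 20 per arm. The change is worth making because it is cheap and the trial has little precision to spare.

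**What to change.** Name as-randomised disorder type as a fixed factor in the primary MMRM and in the continuous secondary models, with change from baseline as the response. If baseline is kept as a repeated visit, include stratum by visit, because a main effect alone leaves the change contrast unaltered. In the disorder-specific scales (LSAS-SR, PDSS, PSWQ) the factor will have few levels, and it drops out where only one remains.

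State how sparse levels are pooled, including unspecified with other specified anxiety disorder, by a rule set before unblinding. Do not make the stratum's inclusion depend on a test of baseline differences.

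The Results section says data collection has ended and analysis is under way, but not whether allocation has been unblinded. If it has, report the stratum-adjusted model as a labelled sensitivity analysis.

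Cost: five levels use 5 − 1 = 4 degrees of freedom, or about 4 × 2 = 8 with a by-visit term over two post-baseline visits. If diagnosis is not prognostic and strata are sparse, up to about 1–2 points of power are lost. No new data are needed, because diagnosis is established by SCID-5 at screening.

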### Blinding

Given the nature of the interventions, it is not feasible to blind participants in this study. However, to preserve the integrity of the study outcomes, assessor blinding will be strictly maintained. Researchers responsible for evaluating the efficacy and safety outcomes will not participate in the administration of interventions or the randomization process.

### Data Management

All clinical trial-related information, including case report forms, consent forms, and supporting documentation, will be recorded, processed, and preserved to facilitate proper reporting, interpretation, and verification. Records containing participants' personal information will be strictly confidential. In all documents associated with the clinical trial, including case report forms, participants will be identified only by their identification codes and initials, not by their names.

### Monitoring

Monitoring will be conducted to ensure that the clinical trial is executed in accordance with the approved protocol and applicable regulations. This process includes verifying compliance with the protocol, ensuring accurate and appropriate data collection, reviewing consent and re-consent forms, and verifying the proper collection and reporting of adverse events.

### Statistical Methods: Definition of the Analysis Set

The analysis sets for evaluating data obtained in this clinical trial are defined as follows: the Full Analysis Set is in accordance with to the intent-to-treat principle, encompassing all participants who met the inclusion and exclusion criteria, were randomly assigned, and for whom baseline measurements and at least 1 postbaseline primary outcome was obtained. The Per Protocol Set (PPS) includes participants from the FAS who have adhered to at least 75% of the total intervention and do not meet any discontinuation or dropout criteria. The Safety Analysis Set (SAS) comprises all participants who have undergone at least one safety assessment following random assignment.

All data, including efficacy outcomes, will be analyzed using the FAS, with the PPS serving as a secondary analysis group for additional analyses. Safety variables will be analyzed using SAS. Continuous data will be presented as means and confidence intervals, while categorical data will be presented as frequencies and percentages (%). If necessary, initial characteristics of participants measured at screening or baseline may be categorized for subgroup analysis.

Unless specifically stated otherwise, all statistical analyses in this study's results will be conducted as 2-sided tests, with a significance level set at 5%. However, for the analysis of the primary outcome, the significance level will be set at 2.5%. Statistical analyses will be performed using SAS software (version 9.4 or higher, SAS Institute).

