**Primary Outcome**
The primary outcome will be assessed by analyzing changes in the Hamilton Anxiety Rating Scale (HAM-A) scores from baseline to week 8 in two separate comparisons:Between the electroacupuncture-median nerve stimulation (EA-MNS) group and the Usual Care group.Between the electroacupuncture-vagus nerve stimulation (EA-VNS) group and the Usual Care group.Research HypothesisHypothesis 1 [H0 : μ1 = μ2, H1 : μ1 ≠ μ2]μ1: Changes in HAM-A score from baseline to week 8 in the EA-MNS groupμ2: Changes in HAM-A score from baseline to week 8 in the Usual Care groupHypothesis 2 [H0 : μ3 = μ2, H1 : μ3 ≠ μ2]μ2: Changes in HAM-A score from baseline to week 8 in the Usual Care groupμ3: Changes in HAM-A score from baseline to week 8 in the EA-VNS group

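### The flat 2.5% level for each of the two primary comparisons is valid, but Holm's step-down would be more efficient at the same 5% familywise error; an optional, cheap improvement, not an error

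*Protocol article*

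**What the plan says.** Textbox 2 (Primary Outcome) defines the primary outcome as change in HAM-A "scores from baseline to week 8 in two separate comparisons": EA-MNS against usual care and EA-VNS against usual care. Each has its own two-sided null hypothesis.

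The section Statistical Methods: Definition of the Analysis Set sets the general rule that analyses "will be conducted as 2-sided tests, with a significance level set at 5" percent. It then makes an exception: "for the analysis of the primary outcome, the significance level will be set at 2.5" percent. The Primary Outcomes paragraph of the statistical methods adds: "Results will be presented with means, 97.5% CIs, and" P values.

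No step-down, hierarchical or alpha-recycling rule is stated. On size, the Sample Size section says "the final sample size was adjusted to 20 participants per group, yielding a total of 60 participants". It starts from a minimum of 15 per group and gives no effect size, standard deviation or power. Allocation is 1:1:1.

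**The concern.** The article does not name Bonferroni, but two comparisons at 2.5% with 97.5% intervals are a Bonferroni split of 5%. Under that rule, the second hypothesis is still tested at 2.5% after the first has been rejected. It could then be tested at the full 5% without breaching the 5% familywise bound, which is what Holm does.

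The trial is meant to evaluate two distinct interventions, each against usual care, with 20 per arm and no power calculation. The flat rule therefore gives up some probability of establishing the second intervention when both work. Recruitment is complete at 60, so the sample cannot supply that power. The testing rule is one of the few places where any could be recovered.

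**Working it through.** **1. The plan's own figure.** 0.05 / 2 = 0.025 per comparison; 2 × 0.025 = 0.05 familywise; 1 − 0.025 = 97.5% for the interval. The stated level and interval agree with each other and with a two-sided Bonferroni split. The article gives no power figure to reproduce.

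**2. The two rules.** Let p₁ and p₂ be the two-sided week-8 P values.
- Flat rule: reject hypothesis k if pₖ ≤ 0.025.
- Holm: reject the hypothesis with the smaller P if it is ≤ 0.025; if so, reject the other if its P is ≤ 0.05.

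Example (invented P values): 0.010 and 0.040. The flat rule rejects only the first. Holm rejects both, with adjusted P values 2 × 0.010 = 0.020 and max(0.020, 0.040) = 0.040.

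**3. Error control under Holm.** If both nulls are true, a false rejection needs the smaller P ≤ 0.025, with probability at most 0.025 + 0.025 = 0.05. If one null is true, a false rejection needs that hypothesis's P ≤ 0.05, with probability at most 0.05. Neither step needs the comparisons to be independent, so the shared usual-care arm does no harm.

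**4. Size of the gain.** Inputs from the article: three equal arms, n = 20, two contrasts against one control. Assumed: standardised effect d, normal data, pooled variance on 3(n − 1) = 57 df. The statistic is t = (active mean − control mean) / (s√(2/n)), a stand-in for the week-8 MMRM contrast. Each scenario has 400,000 simulated trials (1,000,000 for d = 0.3), so Monte Carlo error is below 0.1 point.

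Equal effects in both active arms, flat rule → Holm:

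| d | Both shown | Per comparison | At least one |
|---|---|---|---|
| 0.3 | 3.1% → 5.4% | 9.5% → 10.6% | 15.9%, unchanged |
| 0.5 | 11.8% → 18.0% | 24.3% → 27.4% | 36.9%, unchanged |
| 0.65 | 24.9% → 34.4% | 40.8% → 45.5% | 56.6%, unchanged |
| 0.8 | 43.6% → 54.8% | 59.3% → 64.9% | 75.1%, unchanged |
| 1.0 | 69.3% → 78.8% | 80.3% → 85.0% | 91.3%, unchanged |
| 1.2 | 87.9% → 92.9% | 92.9% → 95.4% | 97.9%, unchanged |

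The gain for both is about 2 points at d = 0.3, 6 at 0.5, 11 at 0.8 and 5 at 1.2. The gain per comparison is about 1 to 6 points.

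**5. Unequal effects.**
- d = 0.8 and 0.4: both shown, 13.8% → 20.8%; the stronger arm, 59.1% → 60.0%; the weaker arm, 15.8% → 21.9%.
- d = 0.8 and 0: the working arm, 59.2% → 59.3%; false rejection for the null arm, 2.5% → 3.9%.
- One very large effect and one null: false rejection for the null arm, 2.5% → 5.0%, which is Holm's bound.

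**6. Both nulls true.** Familywise error is about 4.5% under either rule. The two are identical here, because a first rejection needs the same 2.5% threshold.

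**The case against.** The strongest reply is that nothing here is wrong. The hypotheses, the 2.5% level and the 97.5% intervals fit together, the rule is standard, and it was stated in advance. That stands. A reader might infer that the plan's multiplicity control is defective; the documents do not support that.

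A reader might also infer that the flat rule buys nothing in error control. That goes too far. When one arm is ineffective, the flat rule holds that arm's own error at 2.5%, while Holm lets it rise towards 5% and returns almost no power for the working arm. The two arms stimulate different nerves at different frequencies, so unequal effects are plausible.

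Nor should a loss of about 10 points be read as general. It describes the probability of showing both, with equal effects of roughly 0.65 to 1.0. Textbox 2 sets separate hypotheses and nowhere requires both to succeed.

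It is tempting to sharpen the case by using 17 per arm, from the 51 completers in the Results section. The text gives no split by arm. The MMRM also keeps participants who left with some post-baseline HAM-A data, so 17 is not the analysed number.

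Two practical objections also stand. The Results section says analysis is under way, so a late change that makes rejection easier could look post hoc. And the planned intervals match the flat rule's decisions exactly, which they would not do under Holm.

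**Conclusion.** The point holds as an efficiency remark only. The flat 2.5% rule is a valid Bonferroni split. Holm is at least as powerful for every test decision at the same 5% familywise error.

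The benefit is confined to the second rejection. With 20 per arm and equal effects, it adds about 5 to 11 points to the probability of showing both for d between 0.5 and 1.2, and about 2 points at d = 0.3. It adds nothing to the chance of at least one rejection and is negligible when only one arm works. In that last case the null arm's own error rises from 2.5% to at most 5%.

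These sizes rest on assumed effects, because the article supplies none, and on a t test standing in for the MMRM contrast. Correlation with baseline would alter the effective d but not the ordering of the two rules. The change is optional and depends on group results still being unseen, which the documents do not settle.

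**What to change.** If group results have not been seen, obtain institutional review board approval, as the Study Protocol Modifications section requires, and make a dated record. Then amend the two statistical passages as follows:

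- Test the smaller of the two week-8 P values at 2.5% and, if it is significant, the other at 5%.
- Report Holm-adjusted P values.
- Keep the 97.5% confidence intervals as simultaneous intervals.
- State that decisions follow the adjusted P values, so the 97.5% interval for the second comparison may include zero although its hypothesis is rejected.

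If group results have been seen, leave the flat 2.5% rule as it is.

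The cost is a few lines of wording, the approval step and one explanatory sentence in the report. No further data are needed. The price is that the simple match between interval and decision is lost for the second comparison.
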